## Abstract

**Background:**

Temporomandibular disorders (TMD) are a collective term for pain and dysfunction of the masticatory muscles and the temporomandibular joints. The most common types of TMD are pain-related, which may impact the psychological behavior and quality of life. Currently, the most popular methods for the treatment of TMD patients are occlusal splint therapy, often in combination with physical- and/or pharmacotherapy. However, due to the complexity of etiology, the treatment of chronic TMD remains a challenge. Recently, CE-certified systems for non-invasive VNS (transcutaneous auricular vagus nerve stimulation, taVNS) have become available and show positive effects in the treatment of chronic pain conditions, like migraine or fibromyalgia, with which TMD shares similarities. Therefore, it is the main purpose of the study to evaluate the feasibility of daily taVNS against chronic TMD and to assess whether there is an improvement in pain severity, quality of life, and kinetic parameters.

**Methods:**

This study is designed as a single-blinded, double-arm randomized controlled trial (RCT) in a 1:1 allocation ratio. Twenty adult patients with chronical TMD symptoms will be enrolled and randomized to stimulation or sham group. In the stimulation group, taVNS is performed on the left tragus (25 Hz, pulse width 250 µs, 28 s on/32 s off, 4 h/day). The sham group will receive no stimulation via a non-functional identical-looking electrode. Validated questionnaire data and clinical parameters will be collected at the beginning of the study and after 4 and 8 weeks. The compliance of a daily taVNS of patients with chronical TMD will be evaluated via a smartphone app recording daily stimulation time and average intensity. Additionally, the treatment impact on pain severity and quality of life will be assessed with different questionnaires, and the effect on the mandibular mobility and muscle activity will be analyzed.

**Discussion:**

This is the first clinical trial to assess the feasibility of taVNS in patients with chronic TMD symptoms. If taVNS improves the symptoms of TMD, it will be a significant gain in quality of life for these chronic pain patients. The results of this pilot study will help to determine the feasibility of a large-scale RCT.

**Trial registration:**

This study has been registered in the DRKS database (DRKS00029724).

## Introduction

### Background

Temporomandibular disorders (TMD) refer to all neuromuscular and musculoskeletal conditions of the masticatory muscles, temporomandibular joint (TMJ), and the adjacent structures [1], and are mainly characterized by myofascial pain, masticatory muscle pain, and limitations of jaw functions [2]. However, other comorbid types of musculoskeletal pain such as headaches and neck or low back pains frequently occur [3]. The etiology of TMD is multifactorial triggered by biomechanical, neuromuscular, and psychosocial influences [2]. A much higher incidence is reported in women and most prevalent at the age of 30–40 [4]. The role of occlusion in relation to the etiology of TMD is widely considered limited since bruxism appears to be a predisposing and perpetuating factor associated with TMD [5, 6]. Previous studies reported a significant correlation between the occurrence of TMD symptoms and oral parafunctions [7, 8]. The prevalence of treatment need for TMD was estimated to be approximately 15% in the adult population [9], whereas bruxism is even more common with a prevalence of 8–31% [10]. Due to the COVID-19 pandemic, bruxism and orofacial symptoms have increased significantly over the past 3 years [11]. Over 70% of the dentists surveyed in the USA reported a significant increase in the prevalence of bruxism since the onset of the COVID-19 pandemic. Furthermore, the majority of surveyed dentists observed more TMD symptoms as well as chipped and cracked teeth compared to before the pandemic [12]. According to a scientific report released by the World Health Organization (WHO), also the prevalence of anxiety and depression increased by 25% during the first year of the COVID-19 pandemic [13]. Unprecedented stress caused by the lockdown measures and social isolation have been cited as main reasons for this increase. Loneliness, fear of infection, and death as well as financial worries were mentioned as further stressors. Severe mental health problems were most frequently found among younger women (20–45 years) and people with no work and low income [6, 14]. Studies from Israel, Brazil, and Italy [15–17] have shown an increase or worsening of existing TMD symptoms during the pandemic, demonstrating that the relationship between stress exposure and TMD is global [18].

The use of an occlusal splint therapy can be considered the most popular method for the treatment of TMD patients in order to achieve a neuromuscular deregulation and relaxation of the masticatory system [19, 20]. Physical therapy seems to be also effective, especially if the TMD is associated with headache symptoms [21, 22]. The initial management of TMD may include further therapeutic options, such as manual therapy, acupuncture, progressive muscle relaxation, biofeedback, behavioral therapy, or pharmacotherapy (nonsteroidal anti-inflammatory drugs (NSAIDs), tricyclic antidepressants) [21, 23]. However, although the effectiveness of splint therapy has been proven [24], it has limited success when the muscle pain becomes chronic [25]. Moreover, NSAIDs are less effective for chronic masticatory muscle pain [26, 27]. Since pharmacotherapy is often associated with side effects and usually reduces patients’ burden only slightly, new therapeutic methods for the treatment of chronic TMD conditions need to be evaluated.

Vagus nerve stimulation (VNS) was established three decades ago as an implanted device for the treatment of epilepsy [28]. Nowadays, it has gained further interest since it was approved by the Food and Drug Administration (FDA) for the treatment of major depression in 2005 and cluster headaches in 2017 [29, 30]. The electrical stimulation of vagus nerve afferents causes an activation of the nucleus tractus solitarii as primary central relay (Fig. 1). This nucleus projects via multiple neuronal connections to anatomically distributed subcortical and cortical regions leading to an activation of multiple brain areas which are involved in several inflammatory, nociceptive, and emotional processes [31, 32]. However, although vagus nerve stimulation (VNS) is a well-tolerated treatment option [33], due to its invasive nature, potentially simpler, safer, and less expensive therapies are of interest [34]. The most recent development in the field of vagal neurostimulation are transcutaneous devices allowing external stimulation of the vagus nerve with no need for surgical implantation [35]. This transcutaneous auricular vagus nerve stimulation (taVNS) is based on the assumption that some anatomical structures of the ear, like the tragus or the concha, are innervated by branches of the vagus nerve [36]. By using an auricular electrode, the auricular branch of the vagus nerve is stimulated evoking similar therapeutic effects like the invasive VNS [33]. Studies in patients with chronic migraine and cluster headache, conditions in which trigeminal nociceptive afferents also appear to play a role, showed that taVNS had a positive effect on the headache frequency and severity [37, 38]. A recent review summarized the positive effects of taVNS on acute and chronic pain [39]. Similar to the invasive VNS, taVNS also appears to have an antidepressant effect [40, 41], which may be explained by its influence on the autonomic nervous system in terms of activation of the parasympathetic [42]. Patients with TMD often show depressive symptoms and anxiety, characterized as a form of autonomic dysfunction, which in turn is associated with excessive sympathetic activation and concomitant reduced parasympathetic activation [43]. Due to similarities in the pathophysiology of TMD, taVNS with its positive effect on pain perception and the autonomic nervous system may also have a positive impact on symptoms of a chronical TMD disease and may improve the quality of life of these patients.

**Fig. 1 Fig1:**
[figure not shown]
Schematic representation of the effect mechanism of taVNS

### Objectives

#### Primary objectives

Based on the abovementioned observations that taVNS might improve symptoms in both chronic and acute pain, this trial aims to assess the feasibility and compliance of taVNS for patients with TMD. The results will influence the design and methodology of a subsequent large-scale RCT. Specifically, primary study objectives include the following:To collect data to assess the feasibility of the interventionTo investigate the compliance of patients with chronic TMD symptoms treated with taVNSTo evaluate whether this intervention provides clinically relevant treatment effects regarding pain reduction (GCPS score)

#### Secondary objectives

The secondary objectives of this feasibility trial are to detect potential differences in the outcome variables between stimulation and sham group regarding:PHQ-9, GAD-7, PHQ-15, and OHIP-G14 scoresClinical signs of TMD (DC/TMD)The mandibular range-of-motion capacityThe electromyographic activity of the main chewing muscles (EMG of masseter muscle and temporalis anterior muscle)

## Methods

The study will be performed at the University Medical Center Düsseldorf (Department of Prosthodontics) in cooperation with the University Medical Center Knappschaftskrankenhaus Bochum (Department of Neurosurgery). A total of 20 patients will be recruited and examined in three study visits (enrolment, visit 0, and 1) during an observation period of 8 weeks (Fig. 2). Study parameters will be determined at 4-week intervals in relation to the baseline measurement. The attached SPIRIT table (Table 1) shows the study period and explains when interventions and questionnaires will be performed within the study.

**Fig. 2 Fig2:**
[figure not shown]
Study periods

**Table 1 Tab1:** Schedule of enrolment, interventions, and assessments

	Study Period			
	Enrolment	Allocation	Post-Allocation	Close-out
TimePoint	-t1	Visit 0	Visit 1	Visit 2
Enrolment				
Eligibility screen	x			
Informed consent	x			
Questionnaires		x	x	x
DC/TMD examination	x	x	x	x
Kinematics		x	x	x
EMG (Electromyography)		x	x	x
Allocation		x		
Installation of digital protocol app on smartphone		x		
Interventions:				
Stimulation				
Sham-Stimulation				
Assessments:				
Download stimulation diary from smartphone app			x	
Baseline questionnaire		x		
Baseline DC/TMD examination	x	x		
Baseline EMG		x		
Baseline Kinematics		x		
Outcome questionnaires			x	x
Outcome DC/TMD examination			x	x
Outcome EMG			x	x
Outcome kinematics			x	x

### Patients

Patients (≥ 18 years) currently treated for chronic TMD conditions (Grade III or IV of the Graduation of Chronic Pain Scale (GCPS) according to von Korff [44]) at the Department of Prosthodontics of the University Medical Center Düsseldorf will be asked to join the study. A certified dentist with experience in TMD diagnosis will perform the examinations according to the diagnostic criteria for TMDs (DC/TMD) [45, 46]. This study is designed as a single-blinded, double-arm randomized controlled trial (RCT) in a 1:1 allocation ratio as a sham and stimulation group will be compared. A concealed randomization and single blinding will be carried out.

Patients are assigned to one of the two parallel treatment groups using a randomization list, which is based on a random, computer-generated numerical sequence. At the first visit, participants will be assigned to their respective group by a researcher who is not involved in patient recruitment.

#### Inclusion criteria

Chronic temporomandibular disorders (TMD)Age ≥ 18 yearsProvided written informed consent to participate in the trialPositive response to the question, “Do you have pain in the right side of your face, the left side, or both?” [45]Grade III or IV of the Graduation of Chronic Pain Scale (GCPS) [44]No or stable depression for at least 4 weeks

#### Exclusion criteria

Orofacial pain or diagnosis(es) that do not qualify as myalgia, myofascial pain, or arthralgia based on the Diagnostic Criteria for Temporomandibular Disorders (DC/TMD)Severe psychiatric disease (e.g., schizophrenia)Interventions with vagus nerve stimulation or history of vagotomyHistory of relevant cardiac diseases: bradycardic arrhythmia (e.g., sick sinus syndrome), heart failure, condition after myocardial infarctionActive implant, e.g., pacemaker, defibrillator, neurostimulator, cochlear implant or drug delivery device, and ventricular shuntInability to understand the study protocolProgressive neurological disease (e.g., Parkinson’s disease, MS, epilepsy)PregnancyProstate carcinomaPresence of a skin condition like infection, psoriasis, or eczema at the stimulation sitePresence of any anatomical abnormality preventing successful insertion of the ear electrodePresence of any serious medical condition preventing successful study participationAcute tinnitus

#### Abort criteria

Occurrence of an exclusion criteriaOccurrence of severe cardiac arrhythmiasWithdrawal of consent

### Data logging

In order to monitor the patient’s compliance, a smartphone app will be installed with the patient’s consent (available for Android and iOS and connected via Bluetooth to the stimulator) for recording of the daily stimulation time and average intensity. A cloud connection or a registration is not necessary. The app should help the patient to keep track of the stimulation times as stimulation should take place 4 h throughout the day. Although the app shows when the recommended stimulation time of 4 h/day has been reached, the stimulator will not automatically seize stimulation after 4 h. After a stimulation period of 4 weeks, the stimulation protocol will be exported and analyzed with respect to mean daily stimulation time and intensity. If the patient does not have a smartphone, it will be provided for the duration of the study.

### Data protection

All data will be recorded pseudonymously and the link between number and patient name will be stored on a different clinical network storage. The electronically recorded data of this study will be maintained on a password-protected database under the control of the principal investigator. All questionnaires and consent forms recorded on paper will be stored in a locked cabinet in a locked room requiring key-card access. All additional information will be stored without any identification of group assignment on a separate database.

### Outcomes

#### Primary outcomes

The primary outcomes will be feasibility, compliance, and the determination of clinically relevant taVNS treatment effects. Feasibility will include recruitment and retention rates, randomization success, blind-success, compliance with questionnaires and assessment procedures and the occurrence of any adverse events (Table 2). The compliance of 4 h/day taVNS will be electronically logged by an app on the patient’s smartphone. Treatment is considered to be compliant when at least 80% of patients use the stimulator for at least 2 h (mean) per day. Furthermore, this study was designed to detect clinically relevant treatment effects, which we consider to correspond to statistically large effects according to Cohen [47]. An established and widely used, validated questionnaire will be applied to assess the pain severity and activity limitations (GCPS (Graduation of Chronic Pain according to Von Korff [44])).

**Table 2 Tab2:** Key feasibility indicators for progression [48, 49]

Key indicator	Go—proceed with RCT	Amend—proceed with changes	Stop—do not proceed unless changes are possible
**Recruitment rate** *Target figure: 20 participants*	≥ 70% of target number	51–69% of target number	≤ 50% of target number
**Retention rate** *75% of the participants randomized to intervention group will complete outcome measures T0, T1, and T2*	≥ 70% of target number	51–69% of target number	≤ 50% of target number
**Compliance**	≥ 80% of target number use the stimulator for at least 2 h (mean) per day	61–79% of target number use the stimulator for at least 2 h (mean) per day	≤ 60% of target number use the stimulator for at least 2 h (mean) per day

According to power calculations done with G*Power 3.1.9.7 and assuming an alpha error level of 5%, a power of 95%, and a moderate correlation among repeated measures (*r* ≥ 0.5), a sample size of *n* = 18 is required to detect significant intervention (stimulation vs. sham) × time (visit 0, visit 1, visit 2) interaction effects of this size. Assuming a drop-out rate of approximately 10%, a sample of *n* = 20 participants will be initially recruited, 10 in each of the two groups “sham” and “stimulation.” Another just-conducted pilot trial on a taVNS intervention also reaches clinically relevant effects with a similarly small sample size [50]. Furthermore, an investigation of taVNS application in fatigue syndrome reported highly significant effects (*p* < 0.0003) with a sample size of *n* = 15 [51]. Other studies evaluating taVNS application in migraine also used samples of 20 to 30 patients [52–54]. Consequently, a sample size of *n* = 20 appears to be sufficient to achieve statistical significance for clinically relevant (i.e., large) effects of taVNS and was therefore adopted in this study.

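### Table 2's retention row takes a percentage of a percentage: read literally, Go needs only 6 of 10 stimulation completers, and sham drop-out does not count

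*Protocol article*

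**What the plan says.** The section on primary outcomes makes feasibility a primary outcome and lists recruitment and retention rates among its components, with no restriction to one arm. Table 2 in that section turns three indicators (recruitment, retention, compliance) into Go, Amend and Stop bands.

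- **Recruitment row.** The figure under the indicator is "Target figure: 20 participants". Go is "≥ 70% of target number", Amend is "51–69% of target number" and Stop is "≤ 50% of target number".
- **Retention row.** The statement under the indicator is "75% of the participants randomized to intervention group will complete outcome measures T0, T1, and T2". The three bands are worded exactly as in the recruitment row.

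The sample-size paragraph that follows Table 2 plans 20 patients, "10 in each of the two groups", and inflates 18 to 20 ("Assuming a drop-out rate of approximately 10" per cent). No row of Table 2 refers to retention in the sham group.

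**The concern.** In the recruitment row the target is a count, 20, and the cut-offs are fractions of it. In the retention row the target is already a fraction of the arm, so applying the same cut-offs multiplies two percentages. The bands then lie well below what a reader who sees 70% in the Go column would expect. The row also names only the intervention group, so on its wording any number of sham patients could leave without changing the result.

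The stated purpose of the pilot is to inform the feasibility and design of a larger randomised trial. A sham-controlled trial needs both arms to stay. Sham patients use a non-functional electrode for four weeks and are told to keep the intensity below threshold, so their retention is a real feasibility question. A rule that can report Go with 40% loss in the active arm, whatever the loss under sham, gives weak guidance. If the denominator is not fixed, it could also be chosen after the counts are known.

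**Working it through.** **Inputs.** From Table 2: retention target 75% of the intervention group; Go at 70% or more, Amend 51–69%, Stop 50% or less, each of the target number. From the sample-size paragraph: 10 randomised per arm, 20 in all.

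**The parallel row first.** Recruitment: target 20; Go = 0.70 × 20 = 14. Here the figure printed under the indicator is what the percentage multiplies.

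**Retention, same reading.** Target = 0.75 × 10 = 7.5 patients. The Go line is 0.70 × 7.5 = 5.25, so 6 completers. As a share of the arm it is 0.70 × 0.75 = 52.5%.

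| Completers of 10 | % of target (÷ 7.5) | % of arm | Result |
|---|---|---|---|
| 3 | 40.0 | 30 | Stop |
| 4 | 53.3 | 40 | Amend |
| 5 | 66.7 | 50 | Amend |
| 6 | 80.0 | 60 | Go |
| 7 | 93.3 | 70 | Go |

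Rounding the target up to 8 does not move the Go line: 0.70 × 8 = 5.6, again 6.

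**Other readings of the row.**

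| Meaning of the denominator | Calculation | Go from |
|---|---|---|
| 75% of the stimulation arm (literal) | 0.70 × 0.75 × 10 = 5.25 | 6 of 10 |
| All randomised to the stimulation arm | 0.70 × 10 = 7 | 7 of 10 |
| 75% of all participants, if 'intervention group' is loose wording | 0.70 × 0.75 × 20 = 10.5 | 11 of 20 |

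**How often the rule returns Go.** Let X be the number of completers among 10, binomial with true retention p, patients independent. P(Go) = Σ C(10, x) pˣ (1 − p)¹⁰⁻ˣ, summed from the Go line to 10. For p = 0.60 and x = 6 to 10 the terms are 0.2508, 0.2150, 0.1209, 0.0403 and 0.0060. Their sum is 0.633; without the first term it is 0.382.

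| True retention | Go at 6 of 10 | Go at 7 of 10 |
|---|---|---|
| 50% | 0.377 | 0.172 |
| 60% | 0.633 | 0.382 |
| 75% | 0.922 | 0.776 |
| 90% | 0.998 | 0.987 |

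The choice of reading matters little when retention is excellent. It matters most between 50% and 75%, the range in which a progression rule has to discriminate.

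**Sham arm.** Under the first two readings the numerator contains stimulation patients only. With 6 stimulation completers and any number of sham completers from 0 to 10, the row reads Go.

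**The case against.** The best defence is that the table is meant to be tolerant. Recruitment of 14 against a target of 20 is also Go, so a Go line below the stated aim is how the table works. That stands: nothing in the article requires Go to equal 75%, and a 7-of-10 line would be no error merely because it falls short of the target. It does not settle which denominator the retention row uses, or whether its authors meant to accept 52.5%.

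A second defence is that the 6-of-10 figure belongs to one reading. That also stands, which is why the 7-of-10 and 11-of-20 lines are given beside it. The literal reading is the one that the wording and the parallel row support.

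Third, 'intervention group' may be loose wording for everyone. The arms are elsewhere called stimulation and sham, and Table 1 lists both under interventions. Sham losses would then count, but the two percentages would still multiply.

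A reader might infer that the row contradicts the drop-out allowance of about 10%. It does not: one is a planning expectation used to inflate the sample, the other is the loss tolerated before redesign. A reader might also infer that this row alone decides whether the large trial goes ahead. The documents do not say so. Table 2 has three indicators, further feasibility measures are listed in the text, and the abstract says only that the results will help in judging feasibility. Nor does the article say that sham retention will go unreported; the gap is in the decision rule.

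**Conclusion.** The point holds as a badly fixed threshold for one component of a primary outcome. On the literal reading Go is 52.5% of the stimulation arm: 6 of 10 completers, hence up to 40% loss, with sham losses having no influence. On the two other plausible readings Go is 7 of 10 or 11 of 20. At a true retention of 60%, the choice between 6 and 7 of 10 moves the chance of Go from 63% to 38%. These figures rest on 10 patients randomised per arm, as planned, and on independent drop-out.

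Severity is moderate. The row affects neither randomisation, data collection nor the effect analysis, and it is one indicator among several. No statement about lost power is made here: the article gives its effect size only as large, without a number, and this row does not govern the power of the pilot.

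**What to change.** Express the retention cut-offs directly as percentages of all randomised patients, both arms, who complete Visits 0, 1 and 2, without multiplying by the 75% target. One option keeps the printed bands: of 20 randomised, Go at 14 or more (0.70 × 20), Amend at 11 to 13 (55–65%), Stop at 10 or fewer (50%).

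A pooled count alone can hide a one-sided loss: 10 sham plus 4 stimulation completers also make 14. The row should therefore require a minimum in each arm, or at least state that retention is reported for each arm separately. Whether Go should be raised to the 75% target is the sponsor's choice; the table should then say what the 75% is for. The row should also use the visit names used elsewhere in place of T0, T1 and T2.

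The cost is table wording, settled before retention data are examined. No procedure or sample size changes. The drawback is that Go becomes somewhat harder to reach.

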### End of study

#### Data analysis

This trial features a 2 × 3 factorial design with the factors group (stimulation, sham) and time (Visits 0, 1, 2). Main and interaction effects on the secondary endpoints will be statistically tested via a mixed-measures ANOVA. In case the preconditions for ANOVA use are not met, nonparametric alternatives will be employed. Global effects will be further elucidated by appropriate post hoc comparisons between individual conditions (i.e., per group or time point). The significance threshold will be set to *p* < 0.05, corrected for multiple comparisons where needed. Furthermore, estimates of treatment effect size and confidence intervals will be reported in addition to significance testing results. These analyses will provide a treatment effect estimate on each outcome measure. Outcome measures at baseline, 4 and 8 weeks post-intervention will be entered into the model as the dependent variables with fixed effects of study arm, baseline outcome measures, time, and time point by study arm interaction.

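### The claim that n = 20 suffices for clinically relevant, Cohen-large effects is not supported: on the scale that yields n = 18, "large" means the arms diverge by about 1.7 SD

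*Protocol article*

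**What the plan says.** Under Primary outcomes, the protocol article makes the determination of clinically relevant treatment effects a primary outcome, alongside feasibility and compliance. It defines such effects only by reference to a convention: "which we consider to correspond to statistically large effects according to Cohen". No f, d, SD or difference in GCPS units is given.

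The sample-size paragraph in the same section uses G*Power 3.1.9.7 with a 5% alpha, 95% power and "a moderate correlation among repeated measures" (r ≥ 0.5). It states that n = 18 "is required to detect significant intervention (stimulation vs. sham) × time (visit 0, visit 1, visit 2) interaction effects of this size". Allowing for about 10% drop-out it recruits 20, ten per arm. It then concludes that this number "appears to be sufficient to achieve statistical significance for clinically relevant (i.e., large) effects of taVNS".

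The Data analysis section describes a group-by-time design (two arms, Visits 0, 1 and 2) analysed by mixed ANOVA. It also mentions a model with baseline as a fixed effect, and says that effect estimates with confidence intervals will accompany the tests.

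**The concern.** Two different meanings of "large" are run together. The label is conventional for an f of 0.40 and for a two-group standardised difference of 0.8. In the default G*Power routine for a within-between interaction, however, f is defined before the gain from repeated measurement, and f² is then multiplied by m/(1 − r), which is 6 here. An f of 0.40 entered there describes a far wider separation of the arms than 0.8 SD. Because the article prints neither f nor the option, the reader cannot see this, and the text goes on to equate the effect with clinical relevance.

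What is at stake is interpretation. A reader told that power is 95% for clinically relevant effects may take p > 0.05 on the GCPS as evidence that no such effect exists. The same f could also be carried over when the larger trial is sized.

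**Working it through.** **Inputs.** From Primary outcomes: alpha 0.05, power 0.95, r = 0.5 (the lower bound of r ≥ 0.5), two arms, three visits, 1:1 allocation, about 10% drop-out. Assumed, because not printed: f = 0.40 (the conventional large f), sphericity, and the default effect-size option.

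**1. Reproduce n = 18.** In the default option λ = f²·N·m/(1 − r), with df = 2 and 2(N − 2).
- N = 16: λ = 0.16 × 16 × 3/0.5 = 15.36, power 0.924.
- N = 18: λ = 0.16 × 18 × 3/0.5 = 17.28, power 0.953.
- The smallest N reaching 0.95 is therefore 18, and 18/0.9 = 20. The plan's figures reproduce.

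Other inputs that were tried do not return 18:

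| Input | Result |
|---|---|
| f = 0.35, default option | N = 24 |
| f = 0.45, default option | N = 16 |
| f = 0.25, default option | power 0.59 at N = 18 |
| f = 0.40, "as in SPSS": λ = f²(N − 2)(m − 1) | N = 52 (λ = 0.16 × 50 × 2 = 16.0) |
| f = 0.40, "as in Cohen": λ = f²·N·(m − 1) | N = 50 (λ = 0.16 × 50 × 2 = 16.0) |

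**2. Translate f into a between-arm difference.** Let the arms differ by d_t (in SD) at visit t. Then f² is the mean over visits of (d_t − mean d)²/4.
- Pattern (0, d, d) or (0, d, 0): f² = d²/18, so d = 0.40 × √18 = 1.70 SD.
- Pattern (0, d, d/2) or (0, d/2, d): f² = d²/24, so d = 0.40 × √24 = 1.96 SD.

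**3. Power for d = 0.8 SD, pattern (0, d, d) or (0, d, 0).** f = 0.8/√18 = 0.189. At N = 18 and r = 0.5, λ = 0.0356 × 18 × 6 = 3.84.

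| r | Power, N = 18 | Power, N = 20 |
|---|---|---|
| 0.5 | 36.9% | 40.9% |
| 0.6 | 44.9% | 49.6% |
| 0.7 | 57.1% | 62.4% |
| 0.8 | 75.7% | 80.7% |
| 0.9 | 97.0% | 98.3% |

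Simulation (40,000 runs per scenario) gave 37% for N = 18, r = 0.5, and 95% for d = 1.70. With partial wash-out (0, d, d/2), power at N = 18 and r = 0.5 falls to 28.5%. If 0.8 is counted in SDs of the change score, power stays at about 37% whatever r is. For 0.8 raw SD at r = 0.5, 80% power needs 48 analysed patients and 95% needs 74.

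**4. Precision available.** For a baseline-adjusted week-4 difference with 9 per arm at r = 0.5, SE = √(1 − 0.25) × √(2/9) = 0.408 SD. With t(0.975, 15 df) = 2.131, the expected 95% half-width is 2.131 × 0.408 = 0.87 SD.

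**The case against.** **The arithmetic is right and the benchmark is ours.** The plan claims power for an interaction of Cohen-large size, and for f = 0.40 in the default option that is correct. It never names 0.8 SD. This stands so far as it goes: there is no calculation error, and both f = 0.40 and the 0.8 SD yardstick are brought in from outside the text. But the plan does not stop at the interaction f. It equates the effect with clinical relevance and declares the sample sufficient, without giving any difference on which a reader could judge that.

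**r may exceed 0.5.** It may, and 37% belongs to the lower bound. Even so, 95% is reached only near r = 0.9.

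**Other analyses do better.** A baseline-adjusted model, which the Data analysis section also describes, has more power for 0.8 SD with 9 per arm. For the week-4 difference it is about 45% at r = 0.5 and 60% at r = 0.7. For the average of both follow-ups, if the effect is fully sustained, it is 61% and 75%. So it cannot be said in general that a large benefit would be missed more often than found. All four figures remain well below 95%.

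**It is a pilot.** A pilot need not be powered for efficacy. This one nevertheless lists clinically relevant pain reduction among its primary objectives and says that it was designed to detect it.

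**A stronger reading that does not hold.** A reader might infer that a non-significant GCPS result could stop the definitive trial. Table 2 bases progression on recruitment, retention and compliance only and contains no efficacy criterion. Nor does the article say that p > 0.05 will be read as no effect, and it already promises estimates with confidence intervals.

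**Conclusion.** The concern holds as a fault in the sample-size justification, not in its arithmetic. Given the inferred f = 0.40, the default option, r = 0.5 and sphericity, 18 completers have 95% power for arms that diverge by about 1.7 SD (about 2.0 SD with partial wash-out). That is roughly twice a conventionally large two-group difference (1.70/0.8 = 2.1). For 0.8 SD the interaction test has about 37% power at r = 0.5, 57% at r = 0.7 and 76% at r = 0.8. The statement that n = 20 is sufficient for clinically relevant effects is therefore unsupported. These percentages apply to the interaction test and to an effect that appears in full at week 4; gradual or partly lost effects do worse. The consequence is a risk of misreading a null result, not a formal effect on progression.

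**What to change.** Keep n = 20 and change the wording under Primary outcomes:

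- State f, its metric, the G*Power option and the detectable difference. For example: 18 completers give 95% power for a between-arm difference in change of about 1.7 SD at r = 0.5; power for 0.8 SD is about 37% at r = 0.5 and 57% at r = 0.7. The sponsor should confirm that f = 0.40 and the default option were what was entered.
- Delete the sentence that n = 20 is sufficient for clinically relevant effects, and the matching statement that the study was designed to detect them.
- Make the GCPS comparison primarily an estimate: the baseline-adjusted between-arm difference with its 95% confidence interval (expected half-width about ±0.87 SD with 9 per arm at r = 0.5). State that p > 0.05 will not be taken to show the absence of a clinically relevant effect. This builds on the estimates and intervals that the Data analysis section already promises.

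The cost is a less favourable stated power and a few sentences of text. Recruitment, procedures and Table 2 are unchanged.
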